### 4.2 Intervention

#### 4.2.1 Treatment scheme

The study includes a screening, a baseline examination, 16 intervention sessions a' 30 min over 4 weeks, a post-intervention testing, a focus group for the participants of the intervention group and a follow-up call 4 weeks after the end of the intervention.

The duration and number of examinations and treatments (Table 1) will take place in the context of the patients' inpatient interdisciplinary rehabilitation. It is ensured that all study participants receive the same number of treatments in total. In addition, all participants must receive 8 30-min sessions of physiotherapy per week, of which 4 are reserved for the study intervention in group 1 or 2 and represent an additional measure. All therapists will be trained on the study interventions and instructions for participants in both groups and will therefore work according to the same principles.

**Table 1:** Treatment regimen of a (screened possible\*) study participant

| Intervention                | Dosage | Time                                                                      | Duration    |
|-----------------------------|--------|---------------------------------------------------------------------------|-------------|
| Screening*                  | 1x     | After verification of suitability by the investigator and patient consent | 10-15 min   |
| Study inclusion             |        |                                                                           |             |
| Baseline investigation      | 1x     | Day 0 after study inclusion                                               | 75-90 min   |
| Intervention groups 1 and 2 | 16x    | Start on day 1 after the baseline examination                             | 30 min each |

|                          |    |                                                                                                                                           |           |
|--------------------------|----|-------------------------------------------------------------------------------------------------------------------------------------------|-----------|
|                          |    | 4 x per week, 4 weeks in total                                                                                                            |           |

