| Postintervention testing | 1x | 4 weeks after the start of the intervention                                                                                               | 75-90 min |
| Focus group              | 1x | 4 weeks after the start of the intervention, only for intervention group 1, at a time interval of >2 hours from post-intervention testing | 45-60 min |
| Follow-up call           | 1x | 4 weeks after end of intervention                                                                                                         | 15 min    |

\*If one or more exclusion criteria are present after screening, the patient will not be included in the study.

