#### **4.5.1.4 Severity**

The severity levels of the incidents ((S)UE and (S)NW) are defined as follows:

- Mild - Intervention must be interrupted due to the incident, but can be continued the same day or the following day. Consultation with a doctor for treatment is not necessary;
- Moderate - Intervention must be interrupted, can be continued on another day but not immediately the following day. Consultation with a doctor for treatment is necessary.
- Severe - The intervention must be terminated and cannot be continued due to the event (in terms of a drop-out according to chapter 5.4)

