## 5.4 Drop-out of patients (drop-out)

Patients may withdraw from the clinical trial at any time at their own request, early and without giving reasons and without consequences for their future treatment. In addition, patients can be excluded from the study by the investigator for reasons of health risk.

The following points or events also lead to the drop-out of the subject after initial inclusion in the study (in the sense of a classification as drop-out for the biometric analysis):

- No questionnaire scores or assessment scores of interpretable quality.
- Withdrawal of consent to study participation by the study participant within their study integration.
- Any change or adjustment in dopaminergic medication that the investigator decides is no longer compatible with the study objectives - see exclusion criteria.

If, after the start of the study intervention, the patient's health is endangered due to an unexpected deterioration in health or general condition and/or an absolute contraindication to physical training, participation in the study will be terminated immediately and a specialist consulted.

The reason for the patient's withdrawal from the study is documented in the CRF. The study must be continued with the next subject number.

All patients who leave the study prematurely are asked to undergo a final examination in the form of post-intervention testing at the next possible opportunity - if this is possible during the rehabilitation period and if they are in good health - and the results of this examination will be documented in the CRF.

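### Patients who stop for health, a severe event or an incompatible medication change count as drop-outs even if they still consent, and are not held to the week-4 assessment

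*Protocol*

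**What the plan says.** Section 5.4 lists withdrawal of consent as one reason for drop-out among several, so the other reasons can apply to a patient who still consents. Three matter here.

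- **Health stop.** If health is endangered or training is contraindicated, "participation in the study will be terminated immediately and a specialist consulted".
- **Medication change.** The list includes "Any change or adjustment in dopaminergic medication that the investigator decides is no longer compatible with the study objectives". It is introduced as drop-out "in the sense of a classification as drop-out for the biometric analysis".
- **Severe event.** Section 4.5.1.4 sends it to the same rule: "Severe - The intervention must be terminated and cannot be continued due to the event (in terms of a drop-out according to chapter 5.4". Mild and moderate events only interrupt training and are not part of this point.

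Everyone who leaves early falls under one collection rule. They "are asked to undergo a final examination in the form of post-intervention testing", and this is to happen "at the next possible opportunity - if this is possible during the rehabilitation period and if they are in good health". For participants in general, Table 1 in 4.2.1 sets the post-intervention test at "4 weeks after the start of the intervention" and the follow-up call at 4 weeks after the intervention ends. Section 4.3.2 places the call two months after baseline. Section 5.4 does not mention the call.

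Section 5.6.1 states an intention-to-treat analysis in the groups as assigned. It compares ordinal outcomes, including the FGA, by post-intervention minus baseline with a Mann-Whitney test.

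**The concern.** Stopping training and leaving the study are treated as one event. An intention-to-treat comparison needs outcomes from patients who stopped training, at the same time point as everyone else where possible. Section 5.4 asks for a test when it is first convenient, does not ask for the week-4 test if that opportunity came early, and drops the test if the patient is unwell or has gone home.

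The good-health condition is also wider than its protective purpose. It covers the whole battery, although the questionnaires and fall counts need no physical performance. Whether these data exist then depends on the patient's condition, while 5.6.1 justifies its missing-at-random assumptions only by the topic not being sensitive.

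How drop-outs enter the analysis can be left to an analysis plan. A week-4 test, questionnaire or call that was never held cannot be restored by one.

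**Working it through.** **1. How many patients.** Section 4.1.2.3 starts from 30 participants with 10% failure: 30 / (1 - 0.10) = 33.3, rounded up to 34, which reproduces the plan's figure. Expected failures are 0.10 x 34 = 3.4, about 3 over both arms. This also covers consent withdrawals and uninterpretable scores, so fewer than that would be consenting patients who stopped. The 80% retention target in 4.4.14.1 would tolerate 0.20 x 34 = 6.8.

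**2. What data are exposed per patient.** Table 2 has 12 clinical measures at post-intervention: FGA, FGA items with eye tracking, TUG, TUGman, BBS, FSST, 10MWT, PDQ-39, FOGQ, FES-I, BDI-II and falls. The last 5 need no physical test. The call has 3 clinical measures (FOGQ, FES-I, falls), and none needs a physical test. Sections 4.4.10.1 and 4.4.11.1 allow FOGQ and FES-I by interview, and the PDQ-39 section on missing answers mentions interviews. For falls only the period after the stop is exposed: 4.4.13 has intervention-period falls observed as well as asked about, and the weekly study diaries of both manuals record falls in and outside training.

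**3. FGA timing, as an illustration.** The Protocol gives no expected gain. Assume a linear gain of 4 points over 4 weeks (a size borrowed from the MDC in 4.4.1.2), and a test right after the stop. What the patient would score at week 4 depends on what drives the gain. Section 4.2.1 gives "8 30-min sessions of physiotherapy per week, of which 4 are reserved for the study intervention", so there are 32 sessions in 4 weeks, 16 of them study sessions. A stop after week 1 leaves 8 + 3 x 4 = 20 of 32. Stops after weeks 2 and 3 leave 24 and 28.

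| Stop after | Exit value | Week 4: study sessions only | Week 4: all physiotherapy | Week 4: upper bound | Shift in mean of 17 |
|---|---|---|---|---|---|
| Week 1 | 1 | 1 | 4 x 20/32 = 2.5 | 4 | 0; 1.5/17 = 0.09; 3/17 = 0.18 |
| Week 2 | 2 | 2 | 4 x 24/32 = 3 | 4 | 0; 1/17 = 0.06; 2/17 = 0.12 |
| Week 3 | 3 | 3 | 4 x 28/32 = 3.5 | 4 | 0; 0.5/17 = 0.03; 1/17 = 0.06 |

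**4. Three stops after week 1.** If they fall at random over 17 + 17, the chance that all are in one arm is 2 x C(17,3)/C(34,3) = 1360/5984 = 0.23; the chance of a 2:1 split is 0.77. A 2:1 split leaves a net shift of 0 to 3/17 = 0.18. All in one arm gives 0 to 9/17 = 0.53.

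**5. Mann-Whitney scale.** With one week-1 stop and no true difference, the probability that a patient in the affected arm exceeds one in the other arm is 16/17 x 0.5 + 1/17 x Phi(-d/(SD x sqrt 2)). Here d is the shortfall, and changes are assumed normal. For d = 3 this gives 0.479 at an assumed SD of change of 2.04 and 0.488 at 4. For d = 0 it is 0.500.

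**The case against.** The strongest reply is that nothing here is contradictory. Table 1 is the schedule for those who continue, and 5.4 is an exit rule for those who leave. All leavers are already asked for the post-intervention test. The intention-to-treat statement concerns the group in which cases are analysed and does not promise a week-4 value for every randomised patient. In a 34-patient pilot with a preliminary efficacy analysis, the effect is close to nil. This largely stands, and it is why the point is an improvement and not an error.

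Several stronger readings are tempting, but the Protocol does not support them:

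- **That the follow-up call is cancelled.** Section 5.4 is silent on it. The gap is that it does not say the call continues.
- **That fall data are lost altogether.** Falls up to the stop are observed and in the diaries.
- **That exit tests are always early.** A patient who recovers as an inpatient could be tested close to week 4, and the timing effect is then about 0. Leavers who are well and still inpatients complete the whole battery.
- **That a medication change ends all assessments.** That item can be read as an analysis status only, which an analysis plan may settle.
- **That the FGA comparison is materially biased.** The 0.53 figure needs three week-1 stops in one arm, all tested at once, and full gain despite stopping. The 4-point gain is borrowed from a measurement-error figure.

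What does not fall to the reply is the collection rule itself: it permits the loss of data that consenting patients could have given.

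**Conclusion.** The point holds as a low-priority improvement to data collection. No stated figure is wrong, and the sample size stays at 34. About 3 patients are expected to be concerned at most, if the planned failure rate is right. For each, PDQ-39, FOGQ, FES-I, BDI-II and later fall counts are at risk if the patient is unwell or discharged.

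For the FGA the issue is mainly timing. All the illustrated shifts are small against the MDC of 4, and a patient still unwell at week 4 has no FGA under either rule. The direction of any bias is unknown. The share of stops in which consent continues, the timing of exit tests and the course of the gain are not in the Protocol. The FGA figures are therefore assumptions shown as a range.

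**What to change.** In 5.4 and 4.5.1.4, separate stopping training from withdrawing consent. For patients who still consent:

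1. Hold the post-intervention assessment at the scheduled week 4, or at discharge if earlier. Use the exit test at the next opportunity only as a fallback, when week-4 testing is unlikely.
2. Apply the good-health condition to the physical tests only. Still collect PDQ-39, FOGQ, FES-I, BDI-II and falls by self-report or, where allowed, by interview.
3. Make the planned call two months after baseline, so that its date does not depend on when training stopped.
4. Count patients who stopped training but were still assessed separately, so that they do not raise the 80% retention criterion.
5. Leave the choice between exit and week-4 values after a medication change to the analysis plan.

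The rules on when training must stop remain as they are, and unwell patients stay protected from physical tests.

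**Cost.** It is a wording change. The 15-minute call is already planned. Where both an exit and a week-4 test are held, the second battery takes 75 to 90 minutes, so about 3 x 90 = 270 minutes in total if that happened for 3 patients.

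**Downsides.** There is some extra burden on patients who were unwell, some may refuse, and a practice effect is possible if both tests are done. A test at early discharge is still off schedule, and after a medication change the week-4 value includes the drug effect.

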## **5.5 Premature termination of the clinical trial**

The sponsor is entitled to terminate the study prematurely due to relevant medical/administrative reasons. The reasons for discontinuation of the trial will be documented in detail. Patients who are still undergoing treatment at the time of discontinuation of the trial are requested to undergo a final examination in the sense of post-intervention testing at the earliest possible time, which will be documented in the CRF. If an investigator has ethical concerns about the continuation of the trial, this must be reported to the sponsor immediately.

The sponsor is entitled to terminate the clinical trial prematurely if

- the participant recruitment rate is inadequate,
- serious, unresolvable problems occur with the quality of the data collected,
- unforeseeable circumstances have occurred at the respective trial centre that do not allow the continuation of the clinical trial,
- unacceptable risks have occurred (decision after new risk-benefit assessment),
- new scientific findings during the term of the study do not allow the continuation of the study,

The study management can decide on the discontinuation of the study in consultation with the sponsor.

If an investigator has ethical concerns about continuing the study, this must be reported immediately to the sponsor.

## 5.6 Data analysis

### 5.6.1 Statistical data analysis

Statistical data analysis is performed using IBM SPSS software, version 26.0 (IBM Corporation, Armonk, NY, USA) and Tobii Pro Lab Analyser (Tobii, Danderyd, Sweden). The statistical significance level is defined by a p-value of  $<0.05$ . An attempt is made to avoid missing data by inspecting the questionnaires after completion and, in case of unanswered items, asking the study participants to complete them. The number of missing data is noted; due to the less sensitive topic of the study, it is assumed that missing variable values can be assigned to "missing completely at random" or "missing at random". An intention-to-treat analysis is performed for all cases analysed in their originally assigned group.

Descriptive statistics are used for demographic data and primary and secondary outcomes. Counted and nominal scaled data (gender, fall rate, recruitment, retention and adherence rate, number of missing data if applicable, number of adverse events) are reported as whole numbers or percentages. Ordinal scaled variables (MMSE, UPDRS, H & Y, FGA, BBS, PDQ-39, FOGQ, FES-I, BDI-II) are expressed as median (minimum, maximum or interquartile range) and metric variables (TUG, TUGman, FSST, 10MWT, eye movements: Saccade velocity, amplitude, latency, fixation duration) by mean (95% confidence interval, CI or standard deviation, SD). The data is also presented graphically (e.g. by bar charts, box plot or line graphs).

The eligibility rate (%) is the percentage of patients suitable for the study after applying the inclusion and exclusion criteria from the Parkinson's patients treated at the Reha Zentrum Münster during the study period.

The recruitment rate (%) is determined as follows:  $(N_{\text{Consent}}/N_{\text{eligible}}) \times 100$ ; where  $N_{\text{Consent}}$  is the number of participants who signed the informed consent form;  $N_{\text{eligible}}$  is the number of patients eligible for the study based on the inclusion and exclusion criteria.

The retention rate (%) is calculated as follows:  $(N_{\text{completed}}/N_{\text{Total}}) \times 100$ ; where  $N_{\text{completed}}$  is the number of participants who completed the study;  $N_{\text{Total}}$  is the total number of participants in the study.

Adherence rate (%) is determined as follows: (Actual number of exercise sessions/planned number of training sessions)\*100 (Osterberg & Blaschke, 2005).

Eligibility, recruitment and adherence rates are calculated using the Wilson 'score' method propagated by Newcombe together with its 95% CI (Newcombe, 1998). In the case of a proportion close to 0 or 1, a Poisson approximation according to Brown is used. (Brown, Cai, & DasGupta, 2001)..

A test for statistically significant differences between the groups at baseline: for nominal data the Fisher's Exact Test is used, for ordinal data the Mann Whitney-U test and for metric data the T-test for independent samples. A preliminary inferential statistical analysis to detect trends in the effectiveness of the intervention and as a basis for sample size calculation for a randomised controlled trial with sufficient power of at least 80% (based on mean differences (SD) between groups) will be performed. For inferential statistics, metric data are first tested for normal distribution and significant data outliers using the Shapiro-Wilk test, Q-Q plots and histograms. Non-normally distributed data are transformed using suitable transformation (e.g. ln, square root), checked again and analysed non-parametrically if normal distribution is missing.

Differences between the two groups and test times are calculated for ordinal data as follows: New variables are generated from the difference between the post-intervention and baseline data. The difference between group 1 and 2 is determined using the Mann Whitney-U test. For the ordinal variables FES-I and FOGQ, which are also collected at the follow-up call, a Kruskal Wallis test is performed across all groups and test time points. Changes in fall rate (nominal) between baseline, post-intervention and follow-up will be calculated using Chi-Square test. Metric data will be tested for homogeneity of variance (Levene test) as the basic assumption of a 2 x 2 ANOVA, with "time (baseline, post-intervention)" as the within-factor and "group (1, 2)" as the between-factor. If there is no homogeneity of variance, an alternative F-statistic (e.g. according to Welch or Brown-Forsythe) is used. If the basic assumption of sphericity is not met, corrected values are used, e.g. according to Greenhouse-Geisser or Huynh-Feldt. To calculate the differences between the groups and measurement times, a 2 x 2 ANOVA (analysis of variance) is performed, followed by pairwise comparisons (Bonferroni correction for all comparisons) between the groups at measurement times 1 and 2 if statistical significance is present. In the case of failure of the adaptive measures, non-parametric tests are used as described for ordinal scaled data.

The effect size is given by partial Eta squared and standardised effect size (Cohen's d).

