|  | 
during the study period.
 
The recruitment rate (%) is determined as follows:
 <math>(N_{\text{Consent}}/N_{\text{Suitable}})*100</math>; where <math>N_{\text{Consent}}</math> is the number of participants who signed the informed consent form; <math>N_{\text{Suitable}}</math> is the number of patients suitable for the study based on the inclusion and exclusion criteria.
 
The retention rate (%) is calculated as follows:
 <math>(N_{\text{Completed}}/N_{\text{Total}})*100</math>; where <math>N_{\text{Completed}}</math> is the number of participants who completed the study; <math>N_{\text{Total}}</math> is the total number of participants in the study.
 
The adherence rate (%) is determined as follows: (Actual number of exercise sessions/planned number of training sessions)*100 (Osterberg & Blaschke, 2005).
 
Eligibility, recruitment, retention and adherence rates are calculated using the Wilson 'score' method propagated by Newcombe, together with its 95% CI (Newcombe, 1998) In the case of a proportion close to 0 or 1, a Poisson approximation according to Brown is used. (Brown, Cai, & DasGupta, 2001)..
 
A test for statistically significant differences between groups at baseline is performed: for nominal data (eligibility, recruitment, retention, adherence rates, gender) the Fisher's Exact Test is used, for ordinal data (age, H & Y, UPDRS, FGA, MMST, BBS, PDQ-39, FOGQ, FES-I, BDI-II) the Mann Whitney-U test and for metric data (TUG, TUGman, FSST, 10MWT, eye movements: Saccade velocity, amplitude, latency, fixation duration) the T-test for independent samples. Preliminary inferential statistical analysis to detect trends in intervention effectiveness and as a basis for sample size calculation for a randomised controlled trial with sufficient power of at least 80% (using mean (SD) differences between groups) will be performed. For inferential statistics, metric data are first tested for normal distribution and significant data outliers using the Shapiro-Wilk test, Q-Q plots and histograms. Non-normally distributed data are transformed using suitable transformation (e.g. ln, square root), checked
 |

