## 2.5 Alternative hypotheses

**Primary alternative hypothesis:** There is a difference between the effects of an everyday physiotherapy training programme with eye movement training and such a training programme without eye movement training on dynamic balance in people with idiopathic Parkinson's syndrome.

**Secondary alternative hypotheses:** There is a difference between the effects of an everyday physiotherapy training programme with gaze movement training and such a training programme without gaze movement training on functional mobility with and without manual multi-task, static balance, walking speed, health-related quality of life, freezing of gait, fall-associated self-efficacy, depression, fall rate and eye movements during dynamic balance tasks and specific training items in individuals with Idiopathic Parkinson's Syndrome.

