#### **4.1.2.3 Number of participants and sample size**

For this study, 34 people with Idiopathic Parkinson's Syndrome will be included. Of the 34 people with Parkinson's disease, 17 will be randomised to intervention group 1 and 17 to control group 2.

According to Julious, participants per group are considered a minimum sample size for a pilot study. (Julious, 2005) while Browne specifies a number of participants of 30 for a two-arm study. (Browne, 1995). Therefore, to evaluate the feasibility criteria and preclinical effects of the experimental intervention compared to the conventional control intervention, a sample size of 34 is aimed for, based on 30 participants, including an expected failure rate of 10% and using the formula  $N = n / (1 - (z/100))$ . Here, n is the number of participants (30) and z is the expected failure rate (10%).

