#### **4.4.1.2 Psychometric criteria**

The MDC is 4 points (Petersen et al., 2017). For individuals with Idiopathic Parkinson's Syndrome, the cut-off value is  $\leq 18/30$  points for identifying an increased risk of falls. The sensitivity is 80.6% and the specificity 80.0%. (Yang et al., 2014). The inter-rater reliability (ICC=0.99; 95% CI = 0.99-1.00) and intra-rater reliability (ICC=0.99; 95% CI = 0.99-1.00) are both excellent (Yang et al., 2016). Test-retest reliability is also very good with an ICC value of 0.86 (Petersen et al., 2017). Cronbach's alpha is 0.94, indicating excellent construct validity. (Yang et al., 2016).

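### The main trial is to be sized for at least 80% power on the difference observed in about 30 pilot patients, a rule that does not deliver that power for small to moderate effects

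*Protocol*

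**What the plan says.** Section 5.6.1 describes a preliminary inferential analysis with two purposes: to look for trends in effectiveness, and to serve as the "basis for sample size calculation for a randomised controlled trial with sufficient power of at least 80% (based on mean differences (SD) between groups". The statistical part of the synopsis repeats this, with "sufficient power of at least 80% (using mean (SD) differences between groups".

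Section 4.1.2.3 sets the size of the pilot: "a sample size of 34 is aimed for, based on 30 participants, including an expected failure rate of 10" per cent, with 17 patients randomised to each arm.

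Neither sizing sentence names an endpoint, a target difference fixed in advance, a confidence limit, or any discount on the pilot's effect. The only FGA benchmark for change is in section 4.4.1.2 ("The MDC is 4 points"). It is given there as a psychometric property and is not linked to the sizing.

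**The concern.** The sentence takes two quantities from the pilot: the difference between groups and the SD. An SD from 30 patients is usable with some caution. A difference from 30 patients is not, because its standard error is as large as many effects one might plausibly expect. If the pilot overestimates the effect, the main trial comes out too small. If it underestimates the effect, the computed trial may be too large to run. Power calculated at the observed difference is therefore not the power at the true difference.

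Informing a larger randomised trial is one of the study's stated aims (sections 2.1 and 2.3). At stake is a main trial described as having at least 80% power when its real power is often well below that. No pilot participant's safety is affected.

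**Working it through.** **Inputs from the protocol.** Two-sided 5% level (section 5.6.1 sets 0.05; two-sided is inferred from the non-directional alternative in section 2.5). Power target 80%. Allocation 1:1, 34 randomised, 30 expected evaluable.

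**Assumptions, because the protocol gives no figure.** True standardised difference d from 0.2 to 1.5; normal outcome; 15 or 17 analysed per arm.

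**Step 1: the plan's own figure.** N = n / (1 - z/100) = 30 / 0.90 = 33.3, rounded up to 34. This reproduces.

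**Step 2: precision of the pilot difference.** In SD units the standard error is sqrt(2/15) = 0.365. The 95% confidence half-width is t(0.975, 28) x 0.365 = 0.75 SD with 15 per arm, and 0.70 SD with 17 per arm.

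**Step 3: the sizing rule.** n per arm = 2 x (1.96 + 0.842)^2 / d_obs^2 = 15.7 / d_obs^2. If the true effect were known, this would give 175 per arm at d = 0.3, 63 at 0.5 and 25 at 0.8.

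**Step 4: one illustration.** Suppose true d = 0.5 and the pilot shows 0.8, which is less than one standard error too high (0.3 / 0.365 = 0.82). The rule gives 25 per arm where 63 are needed. True power is about Phi(0.5 x sqrt(25/2) - 1.96) = Phi(-0.19), or about 42%.

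**Step 5: average over pilots.** 400,000 pilots were simulated per setting. The main trial was sized by Step 3 when the observed difference favoured the intervention, and its power was evaluated at the true d. The ranges cover 15 and 17 per arm and, from d = 0.3 to 1.0, also the formula with one extra patient per arm. Exact t-test sizing agrees within about 1 point.

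| True d (assumed) | Mean true power | Pilots whose main trial has at least 80% power |
|---|---|---|
| 0.2 | about 50% | about 30% |
| 0.3 | 59-60% | about 37% |
| 0.5 | 69-70% | 45-46% |
| 0.8 | 75-77% | 49-51% |
| 1.0 | 77-79% | 51-55% |

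At d = 1.2 mean power is 78% (81% with the extra patient), and at d = 1.5 it is 80% (84%).

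If the main trial is always run, using the absolute observed difference, the means with 15 per arm are 65% (d = 0.3), 72% (0.5), 75% (0.8) and 77% (1.0).

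**Step 6: where the loss comes from.** With the target fixed and equal to the truth, and only the SD taken from the pilot, mean power is 78-79%. Most of the shortfall therefore comes from using the observed difference. Entering the SD at its one-sided 80% upper limit multiplies it by 1.139 (28 degrees of freedom). Mean power is then about 87%, and 80-84% of pilots lead to at least 80%, again only if the target equals the truth. The cost in sample size is 1.139^2 = 1.30.

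**Step 7: why the 4-point MDC is no substitute target.** Taking it as a 95% MDC with the ICC of 0.86 from section 4.4.1.2: SEM = 4 / (1.96 x sqrt(2)) = 1.44; SD = 1.44 / sqrt(0.14) = 3.86; so 4 points is d = 4 / 3.86 = 1.04. With the SD at 1.139 x 3.86 = 4.39, n is about 20 per arm. Such a trial has about 34% power at a true d of 0.5 and about 15% at 0.3, which is worse than the rule in question.

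**The case against.** The protocol does not write out an algorithm. The analysis is called preliminary, it is only a basis for a calculation, and the main trial's own protocol will have to justify its sample size. This limits the severity, since nothing in the pilot's conduct or data changes. It does not remove the point: the document names the observed between-group difference twice, attaches a power level to it, and adds no safeguard. This is a stated rule, not a detail left open for a later plan.

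The size of the shortfall depends on an effect the protocol never gives, and on the assumption that a main trial follows only a favourable pilot difference. Both are fair points. Running the trial regardless of sign raises the mean at d = 0.3 to 65% but does not reach 80%.

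A reader might infer three stronger things.

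- That the main trial is bound to be underpowered. The figures do not support this: for true effects of about 1.0 SD and above, mean power is close to nominal.
- That a promising programme would be abandoned after a chance zero or negative difference. The protocol does not say so: the criteria for a larger study in section 4.4.14.1 are recruitment, retention, adherence, safety and acceptance, with no efficacy threshold.
- That fixing a target in advance secures 80% power. It does not: the favourable figures in Step 6 assume that the target equals the true effect.

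**Conclusion.** The point holds in a bounded form. The power level attached to the observed-difference rule is not a property of that rule for small to moderate effects. Under the stated assumptions, mean true power runs from about 50% at d = 0.2 to 77-79% at d = 1.0. The promised 80% is met in about 30% of pilots at the low end and about half at d = 1.0. Because these figures rest on assumed true effects, they should be read as a range and not as the power this main trial will have.

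A related mismatch adds to the case. Section 5.6.1 treats the FGA as ordinal, with medians and a Mann-Whitney test on change scores, while the sizing sentence uses means and SDs. If the FGA is the main trial's primary endpoint, the sizing method and the planned test should agree.

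The change should be made, but it does not bear on whether the pilot can proceed.

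**What to change.** In section 5.6.1 and the synopsis, replace the bracketed phrase (in the synopsis, "using mean (SD) differences between groups") with wording to this effect:

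*The main trial will be sized on a target difference in its primary endpoint, justified as clinically important and fixed before unblinding and before any comparison of the groups. It will not be sized on the difference observed in this pilot, nor on the FGA minimum detectable change, which is a measurement-error threshold. The pilot supplies the SD, entered at an upper confidence limit (for example the one-sided 80% limit, about 1.14 times the observed SD with 28 degrees of freedom). The observed difference will be reported with its 95% confidence interval as a plausibility check only. Power will be stated as 80% for a difference of X, by a method that matches the main trial's planned test.*

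The mention of group comparisons is needed because section 4.1.5 places unblinding after the analysis is finalised.

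The cost is wording in two places, no new data, and a clinical justification for X. The computed sample size is about 30% larger than with the plain SD. The power claim then holds at the target; it does not guarantee 80% if the true effect is smaller.
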